### Assessment of data

After browser-based data entry, the data are automatically checked for completeness and internal plausibility by software-based internal rules. Missing or implausible items create warning messages. The data is usually entered after seeing the patient in the outpatient clinic of the respective institution. Missing data will be handled according to the intended analysis. There is currently no external monitoring for the GerPaCyst Registry. Data are collected prospectively via standardized physician-completed questionnaires. Diagnosis will be made according to the standardized criteria outlines in the aforementioned guidelines. Regular quality control is performed by semiannual study meetings of the entire study group. Through these periodic audits harmonized data collection is ensured, combined with the use of the electronic database that automatically identifies and flags incomplete case forms. The GerPaCyst steering committee recognizes that some methodological aspects may require refinement during implementation. Any such changes will be documented and reported. Specifically, laboratory analyses and parameters used in risk models, as well as imaging parameters, may be subject to change over the course of the study.

For building a multi-omics risk stratification model for pancreatic cyst progression, we will utilize deep learning methods. First, we will ensure data processing and integration and preprocess data by normalization (proteomics, genomics, metabolomics, etc.) and harmonization. Data will further be integrated by feature selection and dimensions will be reduced. Then deep learning will be integrated such as neuronal networks. These calculations will be performed by designated bioinformaticians.

### Database structure

GerPaCyst is based on a web-based REDCap data entry system for the systematic collection of patient data, which was developed by Vanderbilt University [19]. Data entry is paperless and performed directly on-site at the respective medical facility (clinic/practice) via an Internet browser. The REDCap implementation meets all requirements of Good Clinical Practice (ICH-GCP) as well as European data safety regulations. Corresponding certificates for data security are available. The system is operated on a server of the computer center of the University of Lübeck and is thus subject to strict access control. Data is collected in pseudonymized form. Pseudonymization keys are kept separately from the database at the participating institutions.

Duration of observation per patient is up to a maximum of 20 years or until the occurrence of an event defined as end of follow-up or death. The study start was the fourth quarter of 2021 and is still ongoing. Centers are still being initialized at the moment.

Entered variables include baseline characteristics such as data on comorbidities like arterial hypertension, diabetes mellitus, chronic obstructive lung disease, medical history of cancer, family history and past medical history. Also, data on perioperative characteristics, if applicable, will be collected. Imaging modalities on the most prominent cysts will be collected at each follow-up. We will perform a quality-of-life questionnaire (EQ-5D-5L) at enrollment and at end of follow-up or surgery [21]. Cyst fluid analysis/molecular characteristics will be collected, if available (S1 Table).

### Statistics

The data required for the respective research question are compiled into an anonymized project-specific evaluation data set with special consideration of the resulting re-identification risk, if any, and made available for the research project. The GerPaCyst study group decides on the provision of the evaluation data sets for scientific evaluation.

For the development of risk models, we aim to utilize neuronal networks with elastic-net regression using R. ROC-Curves will be built for candidate risk variables. According to our and the experience of others, sample size should be ten to 20 times higher than the number of trainable parameters. As of now, we are planning to include 157 variables plus imaging and biomarker profiles (about 40 different parameters). Our sample size should therefore be at least 4000 patients (200x20). To achieve adequate participant enrolment, this study was set up as an international multicenter study. Descriptive data will be evaluated with R or SPSS according to the data characteristics. Nominal data will be evaluated with frequencies and percentages and differences with Chi-square test or the Kaplan-Meyer methods if pertaining to survival. Continuous data will be evaluated by median and interquartile range, differences between two groups will be calculated by Mann-Whitney U Test. Kaplan-Meyer approximation will be used for survival analyses. P-value will be set at p < 0.05.

The further exact analyses will be defined in a Statistical Analysis Plan (SAP) prior to the corresponding evaluation. However, to ensure appropriate analyses, the nature of the data must be considered. For this reason, descriptive analyses will be conducted, from which new hypotheses and questions will arise. Potential systematic biases must be identified and accounted for in the analyses. To account for interobserver variability in radiological data sets, each time a scientific question is raised, it is followed by a review of the imaging data supplied. Other important decisions include defining subgroups of interest (e.g., patient groups that are usually excluded from RCTs) or pooling similar therapies (e.g., when there are only a few patients in individual therapies) and dealing with missing values in registry data. Some of the questions result in periodic evaluations. Other questions arise due to the ongoing, observational process only during the study, which then result in supplementary SAPs. Answering questions that arise only in the course of the study is one of the great advantages (and difficulties) of registry studies [22].

Only the ITSC of the University of Lübeck and the leaders of the GerPaCyst study group or persons appointed by the study group, such as staff of the Chir-NET office of the University Hospital Schleswig-Holstein, have access to the complete data set.

The GerPaCyst registry has been established to be used together with the StuDoQIPancreas Registry, if necessary and for facilitating data use and transfer within Germany, but also internationally. Accordingly, many items have been adapted from the StuDoQIPancreas registry [23].

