## Introduction

Cystic lesions of the pancreas can either be neoplastic or non-neoplastic. Neoplastic cystic lesions include intraductal mucinous papillary neoplasms (IPMN), mucinous cystic neoplasms (MCN), serous cystic neoplasms (SCN) and solid pseudopapillary tumors (SPPT) and make up 90% of all neoplastic cystic tumors of the pancreas [1]. Depending on the entity, pancreatic cysts bear malignant potential that is associated with outcomes comparable to pancreatic cancer [2].

However, diagnostic accuracy remains limited [3]. The accuracy of cross-sectional imaging varies between 39.5% and 46%.

Pancreatic cysts occur in up to 45% in the German population [4]. The incidence is roughly 13% in Germany and the management of pancreatic cysts has therefore become a highly relevant clinical issue. Recent improvements in high-resolution imaging that make their detection more frequent stands in contrast to treatment algorithms that remain highly controversial in the absence of high- quality controlled studies. Between 2012 and 2018 international guidelines for the treatment of pancreas cysts were published [5–8]. All these guidelines make different recommendations on surveillance of small cysts after five years [9].

However, most of these recommendations are under the bias of retrospective surgical series and observational studies [10,11]. Thus, they probably overestimate the potential for malignancy. Analyses that go beyond five or even ten years hardly exist, which makes it difficult to predict the biology of these entities [12]. Furthermore, the knowledge about the long- term risk of IPMN developing in pancreatic cancer is contradictory. Crippa et al. reported an overall risk of 3.7% of IPMNs to develop into pancreatic cancer [13]. Choi et al. reported that a low risk IPMN (lesion without main pancreatic duct involvement or mural nodes) has a 7.8% chance after 10 years to progress into pancreatic cancer and a high-risk IPMN (mural nodes and dilatated main pancreatic duct) has 25% chance after 10 years to progress into pancreatic cancer [14].

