### Trial status

11 university hospitals throughout Germany are currently participating in this study. The first patient was entered in December 2021 and the study is ongoing. It is an interdisciplinary cooperation of surgeons. radiologists and gastroenterologists. At least 5000 patients are planned to be recruited from gastroenterology and surgical departments. Baseline characteristics such as metabolic/endocrine diseases, risk factors and family history, as well as pancreatic cyst data including MPD diameter, enhanced mural nodules, calcifications and the quality-of-life EQ-5 questionnaire will be assessed during index visit and follow-up. Biospecimens like blood, cyst fluid and cyst cytology will be collected, if needed.

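### The minimum of 4000 patients comes from counting input variables as trainable parameters, so it does not follow from the protocol's own rule for the planned neural network

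*Protocol article*

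**What the plan says.** The protocol article gives one quantitative basis for its primary goal, the individual risk models. It stands in the Statistics section and has three steps.

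- The rule: "sample size should be ten to 20 times higher than the number of trainable parameters".
- The count put into it: "we are planning to include 157 variables plus imaging and biomarker profiles (about 40 different parameters", that is about 197, rounded to 200.
- The result: "Our sample size should therefore be at least 4000 patients (200x20".

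The model is named in the same section: "we aim to utilize neuronal networks with elastic-net regression using R". Assessment of data describes it as deep learning: "For building a multi-omics risk stratification model for pancreatic cyst progression, we will utilize deep learning methods". That section places feature selection and dimension reduction before the network step: "Then deep learning will be integrated such as neuronal networks". It does not say how many features remain.

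The Abstract (Results) asks for a model for each included cyst entity. The primary outcome is binary: high-grade dysplasia or invasive cancer during follow-up, or neither. Trial status gives a second figure: "At least 5000 patients are planned to be recruited from gastroenterology and surgical departments".

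**The concern.** The rule is written for one quantity and fed another. A trainable parameter is a fitted weight or bias. An input variable contributes one weight in a regression, but one weight per hidden unit in a network. Counting 200 inputs as 200 parameters therefore sizes a regression, while the sentence presents the result as the size needed for the network.

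This is the only stated justification for the sample size behind the primary goal. A reader would conclude that a network on the listed variables has 20 patients per parameter, and the text does not establish that. The article also gives no expected number of events, although with a rare binary outcome the events carry most of the information about risk. An analyst who took 4000 at face value could fit a model much larger than the data support.

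**Working it through.** **Inputs.** From Statistics: 157 variables, about 40 imaging and biomarker parameters, a multiplier of 10 to 20, and 4000 patients. From Trial status: 5000 patients. From the Introduction: 3.7% overall ("reported an overall risk of 3.7% of IPMNs to develop into pancreatic cancer"), and 7.8% (low-risk) and 25% (high-risk IPMN) at 10 years. From the Discussion: 9% over five years.

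**Step 1: reproduce the plan's figure.** 157 + 40 = 197, and 197 × 20 = 3940. With rounding, 200 × 20 = 4000. The multiplication is correct.

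**Step 2: the model for which that count is right.** A single-layer model with 197 inputs has 197 + 1 = 198 parameters, and 4000 / 198 = 20.2 patients each. For elastic-net regression the rule is met at its upper end.

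**Step 3: the planned network.** The article gives no architecture, so take the simplest as an assumption: P inputs, one hidden layer of h units, one output. Parameters = P·h + h + h + 1 = P·h + 2h + 1. With P = 197:

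| Hidden units | Parameters | Patients per parameter at 4000 | At 5000 | Patients required (10× to 20×) |
|---|---|---|---|---|
| 1 | 200 | 20.0 | 25.0 | 2,000 to 4,000 |
| 2 | 399 | 10.0 | 12.5 | 3,990 to 7,980 |
| 3 | 598 | 6.7 | 8.4 | 5,980 to 11,960 |
| 5 | 996 | 4.0 | 5.0 | 9,960 to 19,920 |
| 10 | 1,991 | 2.0 | 2.5 | 19,910 to 39,820 |

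Under the rule, 4000 patients allow 4000/20 = 200 to 4000/10 = 400 parameters, and 5000 allow 250 to 500. With all 197 inputs, either total stops at two hidden units.

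**Step 4: a network on reduced inputs.** As an illustration, 20 retained inputs and 10 hidden units give 20·10 + 20 + 1 = 221 parameters, and 4000 / 221 = 18 patients each. The rule is then met.

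**Step 5: models per entity.** Four separate regressions on the full list have 4 × 198 = 792 coefficients, an average of 4000 / 792 = 5.1 patients each. An entity would need 198 × 10 = 1,980 patients of its own to reach the tenfold bound. The article does not split 4000 by entity.

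**Step 6: events, as a separate question.** Events = 4000 × rate, divided by the 200 variables counted:

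- 3.7%: 148 events, 0.74 per variable
- 7.8%: 312 events, 1.56 per variable
- 9%: 360 events, 1.8 per variable
- 25%, if every patient were high-risk: 1000 events, 5.0 per variable

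These totals are for all entities together.

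**The case against.** The strongest reply is that Assessment of data plans feature selection and dimension reduction before the network, and that Statistics plans elastic-net. The network may then be small enough, and its details may properly belong in a later analysis plan. Step 4 shows that this can be so, and the missing architecture is not itself the fault here. But 4000 is computed from the full, unreduced list. If the inputs are reduced, 200 is not the network's parameter count; if they are not, 200 is too low for more than one hidden unit. In neither case does the article's derivation fit the network.

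Several stronger readings are tempting and are not supported:

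- *The plan breaks its own rule by counting patients instead of events.* The rule is written for sample size, so counting patients complies with it. Events per variable is a separate methodological criterion.
- *The shortfall is large.* That depends on the architecture. The 1,991-parameter case assumes ten hidden units on all inputs.
- *4000 patients cannot support the model, and it will overfit.* In simulations with 197 pure-noise predictors and 4000 patients, an unpenalised logistic fit shows an apparent AUC of 0.81 with 148 events and 0.73 with 312. Nobody plans that model. Cross-validated elastic-net gave about 0.54 in both settings. Neither result describes a network.
- *The 4000 and 5000 contradict each other.* A modelling minimum of at least 4000 is compatible with a recruitment plan of at least 5000. The article only leaves their relation unstated.

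**Conclusion.** The derivation is wrong as written. About 200 input variables are not the number of trainable parameters of the planned neural network, so 4000 does not follow from the stated rule for that model. It does follow for a penalised regression on the listed variables, pooled over entities. With all inputs and one hidden layer, the tenfold bound is lost from three hidden units on, at 4000 and at 5000 patients. Whether the network after feature selection meets the rule cannot be determined from the article.

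The event count is a further limit on the model: about 148 to 360 events in 4000 patients, at most 1000, or 0.7 to 5 per counted variable before the split by entity.

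Assumptions: one hidden layer with one output, and cited IPMN or malignancy rates standing in for high-grade dysplasia or cancer in all four entities. The registry also takes patients scheduled for surgery and counts high-grade dysplasia, so these rates may understate events. The cited rates also refer to different follow-up times.

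**What to change.** Reword the Statistics section; do not enrol more patients.

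1. State that, under the protocol's own rule, 4000 patients support about 200 to 400 trainable parameters, and that this justifies the penalised regression on the listed variables pooled over entities, not an unreduced network.
2. Limit the network's weight count, after the planned feature selection, to that number and state it, or label the network exploratory.
3. Report the expected number of events overall and per cyst entity, with the rates assumed.
4. If it is what is meant, say that 4000 is the modelling minimum and 5000 the recruitment plan.

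The cost is a less favourable sample-size claim and a smaller network. No additional patients or data are needed.

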### Dissemination policy

Trial results will be communicated with all participating centers on a regular basis including half-yearly meeting sessions at the German Pancreas Club and the German Visceral Medicine meetings (AG Pankreas DGVS). In addition, 4-monthly group meetings will be held virtually in order to communicate possible protocol changes or interim-results. Publication will be decided upon by the steering committee and author inclusion will be based on patient inclusion: up to 10 patients per year: 1 author from each center, 10–20 patients per year: 2 authors per center, etc. Requests for data analysis of the whole cohort can be send to the steering committee for evaluation. The full protocol has been uploaded to the German clinical trial registry (www.drks.de). Participant-level dataset and statistical codes can be obtained from [name].

### Biological specimens

Blood samples or cyst (fluid) biopsies or surgical specimens will be collected at the participating centers, if available and will possibly be used for genetic and molecular analysis in ancillary studies in the future.

### Appendices

Informed consent (Currently in German).

## Discussion

More than twenty years after the first introduction of intraductal papillary mucinous neoplasms (IPMN) by the World Health Organization (WHO), we still struggle to treat not only IPMNs, but most pancreatic cysts. The increasing frequency of detection caused by the rising number of radiology imaging exams will make this an even more pressing issue in the not so far future.

A large surgical series of 577 branch-duct IPMNs (BD-IPMN) found that at a median follow-up of nearly seven years, almost 50% of BD-IPMNs progressed over time with 34% of patients having either worrisome features or high-risk stigmata at the end of follow up [10]. In contrast, a radiologic group found no development of malignancy in a group of 49 patients with BD-IPMNs less than 2 cm in diameter [24]. Similarly, in an Asian study only 9% of 722 patients developed malignancy over a five-year follow up-period [25]. A recent large study from Verona showed that the risk of developing malignancy in presumed BD-IPMN, that are stable over five years and less than 30 mm in size was comparable to that of the general population in the same age group. They even proposed to discontinue surveillance in patients older than 75 years [26]. However, the median follow-up was less than five years in this study. Furthermore, the discrepancies between these studies might be attributed to the different sources of patients (from surgery, radiology and gastroenterology separately).

Another point of discussion in the treatment of pancreatic cysts are main-duct IPMNs and the questions if we should resect all of them, even in old and frail patients. Crippa et al. found that the impact on survival was low, even in those IPMNs with a high malignancy rate [27]. Mucinous cystic neoplasms are to be resected, if they are larger than four centimeters [28]. But MCNs under four centimeters also had a malignancy rate of 43% in a retrospective study by Hohn et al. [29]. These recommendations are also based on retrospective surgical series, which might overestimate the rate of malignancy.

Based on data of pancreatic cancer specimens, clonal evolution from the initiation of tumorigenesis until the birth of the cell giving rise to the parental clone of primary cancer takes an estimate of 11.7 years, an average of 6.8 years from then until the birth of the cell giving rise to the index primary lesion, and an average of 2.7 years from then until the patients’ death [30]. In total, the time of tumorigenesis, here in the example of pancreatic cancer, takes 20.2 years until metastatic dissemination and death. Maybe, we can assume that in the case of pancreatic cysts, the timing is similar or even slower, illustrating the need for long-term follow-up data.

The GerPaCyst registry is therefore designed to include both patients treated by gastroenterologists, radiologist and surgeons to reduce the bias of either surveillance or resected patients. The web-based format and longitudinal study set up is supposed to facilitate inclusion and follow-up and the duration of 20 years will hopefully give the opportunity to include a large group of patients.

With artificial intelligence (AI) on the rise, GerPaCyst will provide a well characterized cohort to perform AI analyses with and to bring pancreatic cyst risk calculation to the next scientific level.

In conclusion, we established a prospective, multicenter, interdisciplinary pancreatic cyst registry to enable the uncovering of long-term pancreatic cyst biology and hope to contribute to improved patient care in the future.

### Trial status

11 university hospitals throughout Germany are currently participating in this study. The first patient was entered in December 2021 and the study is ongoing. It is an interdisciplinary cooperation of surgeons. radiologists and gastroenterologists. At least 5000 patients are planned to be recruited from gastroenterology and surgical departments. Baseline characteristics such as metabolic/endocrine diseases, risk factors and family history, as well as pancreatic cyst data including MPD diameter, enhanced mural nodules, calcifications and the quality-of-life EQ-5 questionnaire will be assessed during index visit and follow-up. Biospecimens like blood, cyst fluid and cyst cytology will be collected, if needed.

## Abbrevations:

IPMN: intraductal papillary-mucinous neoplasia
MCN: mucinous-cystic neoplasia
SCA: serous cystic adenoma
SPN: solid pseudopapillary neoplasia
SPPT: solid pseudopapillary tumors
